**Methods and design:**

Ninety participants diagnosed with KOA will be randomly divided into the acupuncture group, sham acupuncture group, and waiting list group in a ratio of 1:1:1. Except for the waiting list group, the other participants will receive acupuncture or sham acupuncture three sessions per week for 4 weeks respectively. The primary outcome will be the response rate which is defined on an individual basis as at least a 2-point decrease in the numerical rating scale (NRS) of pain at the end of intervention period compared with the baseline. fMRI scans will be performed at baseline and the end of the intervention period to examine the response of various brain regions. The secondary outcomes will include the Western Ontario and McMaster Osteoarthritis Index (WOMAC), State-Trait Anxiety Scale-State Anxiety Subscale (STAI-S), and Stanford Expectations of Treatment Scale (SETS). Pearson’s correlation coefficient will be performed to investigate the changes in brain activity and clinical variables.

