### Blinding

Due to the operation characteristics of acupuncture, the acupuncturists cannot be blinded who will be informed of the grouping of participants before treatment. Participants will be told that they will randomly receive one of the interventions after enrollment. To avoid communication, participants will be assigned to different rooms during the treatment. Since the participants assigned to waiting treatment do not have any intervention, it is impossible to blind them. The outcome evaluators and data statisticians will be blinded to the group allocation, and their responsibility is to collect and analyze the data.

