#### Group C—waiting list

Participants in group C will not receive acupuncture within 4 weeks. After 4 weeks of observation, participants will receive 12 sessions of acupuncture treatment as free compensation.

During the treatment period, some other interventions, such as moxibustion, cupping, and massage, will not be allowed. Participants will withdraw from the study if they violate the protocol. When their pain is unbearable, they will be allowed to take non-steroidal anti-inflammatory drugs. Researchers should keep relevant records.

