### Clinical outcome assessments

The primary outcome will be the response rate, which is defined as a decrease of more than 2 points on the NRS at week 4 compared with baseline [39]. NRS is a line divided into 10 segments. The degree of pain is assessed by 0–10 scores, and 0 score represents pain-free and 10 score represents the worst pain.

The secondary outcomes will be as following: (1) Pain subscale of Western Ontario and McMaster Osteoarthritis Index (WOMAC) scale will be used to evaluate the degree of knee pain of the participants. (2) Function subscale of the WOMAC scale will be used to evaluate the knee joint function. (3) Stiffness subscale of WOMAC will be used to evaluate the stiffness of knee joint. The severity of knee joint will increase with the higher scores of WOMAC. Participants will fill out the WOMAC scale at weeks 0, 2, and 4. (4) Blinding assessment and rescue medicine. (5) Stanford Expectations of Treatment Scale (SETS) will be used to assess participants’ positive and negative expectations of the upcoming treatment and their overall understanding of the purpose of the treatment. Participants will be asked to fill out the SETS scale before weekly treatment. (6) State-Trait Anxiety Scale-State Anxiety Subscale (STAI-S) will be used to evaluate the severity of current anxiety symptoms in participants with knee osteoarthritis. Participants will fill out the STAI-S scale at weeks 0, 2, and 4.

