### Statistical analysis

#### Clinical data analysis

The clinical data will be statistically analyzed by SPSS software (SPSS V.22.0 KO for Windows). Data will be described utilizing the mean (standard deviation) when following a normality assumption and using the median (quartile spacing) when the normality assumption is violated. The percentage (*n* %) will be used to describe the categorical variables. Comparisons between the three groups will be made by repeated-measures analysis of variance or Wilcoxon rank-sum (if normality is violated). For the primary outcome, we will calculate response rates at 4 weeks using the chi-square test. For the secondary outcomes, the mixed effect model and repeated measurement method will be used to compare the continuous variables (including WOMAC, SETS, and STAI-S).

The primary outcome will be performed using the intention-to-treat (ITT) and per-protocol (PP) analysis. ITT is defined as all randomized participants completing at least one post-baseline measurement. PP is defined as all the randomized participants who will not stop treatment prematurely, and complete 4 weeks of treatment, and undergo two MRI scans. The last observation carried forward (LOCF) will be used to estimate the missing values. The data will be considered statistically significant with a level of 0.05, and all hypothesis tests will be two-tailed.

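### The single per-protocol definition does not fit a three-arm design with an untreated arm, and it ties a pain analysis to having two MRI scans

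*Protocol article*

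**What the plan says.** Under Clinical data analysis, the article states: "The primary outcome will be performed using the intention-to-treat (ITT) and per-protocol (PP) analysis". The PP set has one definition for every arm: "all the randomized participants who will not stop treatment prematurely, and complete 4 weeks of treatment, and undergo two MRI scans". The three conditions are joined by *and*, and the waiting list has no rule of its own.

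Three other places describe what the waiting-list arm receives:

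- Abstract, Methods and design: "Except for the waiting list group, the other participants will receive acupuncture or sham acupuncture three sessions per week for 4 weeks respectively".
- Blinding: "participants assigned to waiting treatment do not have any intervention".
- Group C—waiting list: "Participants in group C will not receive acupuncture within 4 weeks", followed by "After 4 weeks of observation, participants will receive 12 sessions of acupuncture treatment as free compensation".

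The outcome to which PP applies is a pain response, under Clinical outcome assessments: "a decrease of more than 2 points on the NRS at week 4 compared with baseline". The exact threshold does not matter here. What matters is that it is an NRS score at week 4 and needs no imaging. The end of the Background makes sham versus waiting list the contrast for the nonspecific effect.

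**The concern.** A PP set should hold the participants who followed their allocated condition. This definition has two faults in that role.

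First, completing treatment is a condition that an untreated arm cannot meet. If the rule is applied as written, the PP set contains acupuncture and sham only. The sham versus waiting-list comparison and the three-group chi-square test then cannot be run in it. If the rule is not applied as written, the analyst must decide what makes a waiting-list participant per-protocol. Advance specification is meant to rule out that choice.

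Second, having two scans is a condition for imaging analyses. A participant who attends every session and gives a week-4 NRS, but misses the second scan, leaves the clinical PP analysis although adherence to treatment was complete. Scanning takes place at a different hospital from the study site (Study setting and recruitment; MRI data acquisition), so a missed scan in an otherwise adherent participant is easy to imagine.

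**Working it through.** **Inputs.** 30 participants per group, 90 in total, 1:1:1 (Randomization). A 20% allowance for dropout and for data lost to head motion (Sample size). The PP conditions and the arm descriptions are those quoted above.

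**The plan's own figure.** The 30 per group is consistent with the article's figure of about 25 raised by 20%: 25 × 1.20 = 30. Dividing instead gives 25 / 0.80 = 31.25, so 32. The sample size is not in dispute here; 30 is used only as the size of each arm.

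**Step 1: apply the PP rule literally to each arm.**

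| Condition | Acupuncture | Sham | Waiting list |
|---|---|---|---|
| Did not stop treatment early | can be met | can be met | no meaning; nothing to stop |
| Completed 4 weeks of treatment | can be met | can be met | cannot be met by week 4 |
| Had two MRI scans | can be met | can be met | can be met; this arm is scanned too |
| Largest possible PP set | 30 | 30 | 0 |

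The total is at most 30 + 30 + 0 = 60, against 30 + 30 + 30 = 90 if PP means completing the allocated 4-week condition. As an illustration, if 20% of each arm were lost, the figures would be 24 + 24 + 0 = 48 against 24 + 24 + 24 = 72. Only the treatment condition empties the waiting-list arm; the scan condition does not.

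The waiting list has one literal way in, through the 12 compensatory sessions. At three per week these would take 12 / 3 = 4 weeks, but they start after the week-4 endpoint. Membership would then depend on events after the outcome was measured.

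**Step 2: the scan condition in the treated arms.** The article gives no rate of adherent participants who miss a scan. Assume a share *m* of 5%, 10% or 15%, and adherence *r* of 80%, 90% or 100%. Participants left per arm = 30 × *r* × (1 − *m*).

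| Adherence | Adherent per arm | m = 5% | m = 10% | m = 15% |
|---|---|---|---|---|
| 80% | 24 | 22.8 | 21.6 | 20.4 |
| 90% | 27 | 25.7 | 24.3 | 23.0 |
| 100% | 30 | 28.5 | 27.0 | 25.5 |

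The loss runs from 24 − 22.8 = 1.2 to 30 − 25.5 = 4.5 per treated arm, and is about 1 to 4 at 80–90% adherence.

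**The case against.** The strongest reply is that the article uses *treatment* loosely for the 4-week period in every arm. Study design places all assessments at baseline and end of treatment, for all participants. The Group C section itself speaks of a treatment period. The limitations paragraph of the Discussion runs observation and treatment together as one 4-week period. The analysis section plans comparisons among three groups. On that usage a waiting-list participant qualifies by completing the 4 weeks. As an account of what the authors meant, this stands. It does not supply a written rule for the arm, and the sentence still conflicts with three statements that this arm has no intervention.

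It can also be said that two scans are a core procedure of an fMRI mechanism trial, so a PP set of full completers is coherent. That is reasonable for the imaging and correlation analyses. It is weaker for a pain responder analysis, because attending a scan does not measure adherence to the allocated condition.

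A reader might infer more than the text supports:

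- *That prohibited co-interventions go unchecked.* They do not. The Group C section has participants withdraw if they violate the protocol, so they would not complete the 4 weeks.
- *That the 20% allowance means up to 6 of 30 adherent participants per arm are lost to the scan rule.* That allowance covers dropouts, who are not adherent, and head-motion losses. The rule requires only that scans took place, so a scan spoiled by motion excludes nobody. Neither component is the adherent participant who misses a scan.
- *That missing a scan is related to outcome and so biases the PP result.* This is possible, but nothing in the article shows it.

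**Conclusion.** The PP definition misfires if it is followed as written. It admits no waiting-list participant by week 4 (0 of 30), so the PP version of the primary analysis would lack sham versus waiting list. It also drops an unknown number of adherent treated participants, about 1–4 per arm if 5–15% of them miss a scan. The first result rests on a literal reading and the second on an assumed rate.

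It would be wrong to conclude that the trial loses its nonspecific contrast. The ITT analysis of the same outcome is unaffected and still compares sham with waiting list. The article applies PP to the primary outcome only, and ties neither the fMRI analyses nor the specific/nonspecific proportion to it. The defect is minor to moderate: a stated rule for a companion analysis that needs correct wording.

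**What to change.** Define PP by arm, as completing the allocated 4-week condition with a week-4 NRS available:

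- Acupuncture and sham groups: the allocated course was completed.
- Waiting-list group: the 4-week observation period was completed without acupuncture.

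Take the two-scan condition out of the clinical PP set. Define a separate imaging analysis set of participants with two scans, used for the fMRI analyses and their correlations with clinical variables. Settle both definitions before the statisticians learn the allocation.

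The cost is wording only. The NRS and the scans are already scheduled, and neither the sample size nor any procedure changes. The downside is that the clinical PP set and the imaging set may differ by a few participants, so the size of each must be reported by arm.

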#### Neuroimaging data analysis

Imaging data will be analyzed using Data Processing Assistant and Resting-State fMRI (DPARSF) toolbox performing on MATLAB 8.6 (Mathworks, Inc., Natick, MA, USA). Data preprocessing will include DICOM format conversion, eliminating the first 10 time points, time correction, head motion correction, spatial standardization (re-sampled to 3 mm × 3 mm × 3 mm), removing linear trend, low-frequency filtering (0.01–0.1 Hz), and regression removal of covariates (head model parameters, cerebrospinal fluid, brain white matter, and the mean whole-brain signals).

After data preprocessing, the amplitude of low-frequency fluctuation, regional homogeneity, functional connectivity analysis, or voxel-wise degree centrality will be performed to investigate the brain responses of different groups. *T* test and repeated-measures analysis of variance will be conducted to investigate the differences in brain regions in each group. Pearson correlation analysis will be used to test the correlation between fMRI imaging data and clinical variables.

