The pain was the most common research topic in acupuncture-related studies published from 1994 to 2014, accounting for about one third of the total publications [30]. A cross-sectional study found that among the common acupuncture adaptation diseases, 5 of the top 10 diseases were related to pain [31]. Knee osteoarthritis (KOA) is high-prevalence chronic osteoarthritis with knee pain and functional limitation [32–34]. The positive response of placebo treatment is a recognized phenomenon in the chronic pain, and the analgesic effect is often comparable to active treatment [35]. For these reasons, KOA is an appropriate model to study the specific and nonspecific effects of acupuncture.

The purposes of this study are to (1) investigate the cerebral mechanism of the specific (true acupuncture vs sham acupuncture) and nonspecific effects (sham acupuncture vs waiting list) of acupuncture based on the brain activities by using fMRI and (2) investigate the proportion of specific and nonspecific effects in acupuncture treatment.

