## Methods and design

### Study design

This is a randomized controlled, parallel study to explore whether specific and nonspecific effects of acupuncture regulate certain brain functional connectivity, respectively. Ninety participants will be recruited in the study, with an average of 30 in each group. Clinical data measurements and fMRI scans will be evaluated at baseline and the end of treatment (Figs. 1 and 2). The study has been approved by the ethical committees of Dongzhimen Hospital Affiliated to Beijing University of Chinese Medicine (NO: DZMEC-KY-2017-53-02) and registered in the Chinese Clinical Trial Registry (NO: ChiCTR1900025799). The protocol will be reported following Standard Protocol Items: Recommendations for Interventional Trials (SPIRIT) statement (Additional file 1).

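### The imaging section leaves the brain measure open among four and words its tests within arms, although the aim is defined by two between-arm contrasts

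*Protocol article*

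**What the plan says.** Under Neuroimaging data analysis, the protocol article lists four resting-state measures joined by *or*: "the amplitude of low-frequency fluctuation, regional homogeneity, functional connectivity analysis, or voxel-wise degree centrality will be performed". The stated purpose is "to investigate the brain responses of different groups". No measure is given priority, and no rule for choosing is stated.

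The next sentence names the tests, a t test and a repeated-measures analysis of variance, which "will be conducted to investigate the differences in brain regions in each group". No between-arm contrast and no group-by-time term is named. A correlation step follows: "Pearson correlation analysis will be used to test the correlation between fMRI imaging data and clinical variables".

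Two other places say what this analysis is for. Study design says that the trial will "explore whether specific and nonspecific effects of acupuncture regulate certain brain functional connectivity". The last paragraph of Background sets the first aim as the cerebral mechanism of "specific (true acupuncture vs sham acupuncture) and nonspecific effects (sham acupuncture vs waiting list) of acupuncture based on the brain activities by using fMRI".

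**The concern.** The imaging section does not commit to the question set elsewhere in the article, in two respects.

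- **Measure.** Study design points to functional connectivity, while the analysis section lets any of four measures serve. If the choice can be made after the maps are seen, the 5% error rate of a single measure no longer describes the chance of a false claim. Reading *or* as one or more of the four does not help, because the multiplicity remains.
- **Comparison.** Both effects in the aim are differences between arms, but the tests are worded within arms. A region that changes significantly under true acupuncture and not under sham has not been shown to differ between the two. Clinical data analysis words its own comparisons as being between the three groups, so the different wording for imaging matters.

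Imaging carries the first aim of the study and is the only basis given for the sample size. A region wrongly labelled specific or nonspecific would go straight into the main mechanistic conclusion.

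**Working it through.** **Inputs from the protocol article**

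- Number of candidate measures: 4 (Neuroimaging data analysis).
- Contrasts in the aim: 2, true versus sham and sham versus waiting list (Background).
- Scans per participant: 2 (Sample size; MRI data acquisition).
- Sizing: 12 participants at a single-voxel level of 0.05, about 25 at 0.000002, 20% dropout, 30 per group (Sample size).

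**Assumed, not in the documents:** the correlation between the four measures (0 to 0.9), a 5% error rate for each measure after its own correction, and the power of a within-arm test (50% or 80%).

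**1. The article's own figure.** 25 × (1 + 0.20) = 30 matches the stated 30 per group. Dividing instead, 25 / (1 − 0.20) = 31.25, gives 32, which is close. So the size rests on the stricter voxel level. That level equals 0.05 / 25,000 = 0.000002, the form of a Bonferroni correction over 25,000 voxels, although the article does not say how it was obtained. The base figures of 12 and 25 cannot be rebuilt, because no effect size or standard deviation is given.

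**2. Free choice among four measures.** With independent measures, the chance of at least one false-positive measure is 1 − 0.95⁴ = 0.185. All four come from the same time series, so they will be correlated. Simulating four equally correlated two-sided z tests (400,000 draws) gives:

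| Correlation | At least one false positive |
|---|---|
| 0 | 18.5% |
| 0.3 | 17.4% |
| 0.5 | 15.6% |
| 0.7 | 13.0% |
| 0.9 | 9.4% |

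The range is therefore about 9% to 19%, against 5% for one named measure.

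A strict voxel level does not remove this. On one map of 25,000 independent voxels, 0.000002 gives 1 − (1 − 0.000002)^25,000 = 4.9%. Over four such maps it gives 1 − (1 − 0.000002)^100,000 = 18.1%.

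**3. Comparing significance between arms.** Suppose two arms have the same true change, and each within-arm test has power p. Exactly one is significant with probability 2p(1 − p).

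- p = 0.80: 2 × 0.80 × 0.20 = 0.32.
- p = 0.50: 2 × 0.50 × 0.50 = 0.50.

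In half of these cases (16% and 25% of trials), true acupuncture is the significant arm, and the region would be read as specific although the arms do not differ.

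**4. Error control if all four measures are kept.** 0.05 / 4 = 0.0125 per measure. The simulated error over the four is then 4.9% at correlation 0 and 2.6% at 0.9.

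**The case against.** The best defence is that the wording is loose rather than wrong. The sentence before the tests speaks of different groups, and Background spells out both between-arm contrasts for the imaging aim. With only two scans, a repeated-measures analysis of variance within one arm is the same as a paired t test (F = t²), so listing both makes most sense if the analysis of variance carries a group factor. This stands as far as it goes. A reader might infer that the trial cannot separate specific from nonspecific brain effects, and the documents do not support that. The design can do it; the analysis text does not commit to it. The 32% and 50% figures apply if the text is followed as written.

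A reader might also infer that every voxel will be tested at an uncorrected 0.05, with thousands of false-positive voxels and false regions almost certain. The documents do not support this either. The sentence "The data will be considered statistically significant with a level of 0.05" stands under Clinical data analysis, and the imaging section gives no threshold. The one place that discusses a voxel threshold, Sample size, relies on the stricter level. A condensed article may leave the voxel or cluster correction, and any adjustment of the correlations, to a fuller plan that is not shown. Their absence is not counted as an error here.

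The imaging is described as exploratory, and Background and the Abstract speak more broadly of brain activities and regions than Study design does. This lowers the weight of the point but does not settle which measure leads. It is also fair that functional connectivity without a seed or network still leaves choices open. That detail can sit in the analysis plan once the lead measure is fixed.

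**Conclusion.** The point holds in two limbs, both resting on what the article states: an open choice among four measures, and tests worded within arms for an aim defined between arms. The first raises the chance of a false-positive measure from 5% to about 9% to 19%, assuming that each measure is itself controlled at 5% and that correlations lie between 0 and 0.9. The second, if followed literally, gives a spurious difference between identically changing arms in 32% to 50% of trials, assuming within-arm power of 80% to 50% and independent arms. The change is worth making, since it concerns the first aim. It does not touch the primary outcome, the response rate on the pain scale.

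**What to change.** In Neuroimaging data analysis, or in the analysis plan before the imaging data are analysed:

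1. Name functional connectivity, the measure in Study design, as the lead imaging measure and label the other three exploratory. Alternatively keep all four on an equal footing and control error over them, for example at 0.0125 each.
2. Replace the within-group wording with a test of pre-to-post change by arm (group-by-time) for the two contrasts in Background: true versus sham, and sham versus waiting list. Within-arm maps can remain as description.
3. State a whole-brain corrected threshold for these contrasts that is consistent with the strict level used under Sample size.

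The cost is wording; the scans and participants stay the same. The downside is fewer significant regions. With equal variance and n per arm, the difference between two arms' changes has a standard error √2 (about 1.41) times that of one arm's change, and a corrected threshold is harder to pass.

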### Randomization

In this study, KOA participants will be randomly divided into acupuncture group, sham acupuncture group, and waiting list group in a ratio of 1:1:1, with 30 participants in each group. The random sequence will be generated by an independent professional statistician ([name]) who is not involved in the study with the software SAS 9.3 (SAS Institute, Cary, NC, USA) using block randomization. The random numbers will be stored by a fixed non-involved person. When the eligible participants are randomly assigned, the random number will be told by the fixed person to the acupuncturists via a short message.

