### Sample size

According to previous neuroimaging studies, in order to calculate statistical power for group-level fMRI studies, a sample size of 12 participants were required to achieve 80% power at the single voxel level when *α* = 0.05, and about 25 participants were required for a stricter threshold of *α* = 0.000002 [37, 38]. In this study, considering a 20% dropout rate and loss of data due to head motion, we plan to recruit 30 participants in each group. Each participant will receive 2 fMRI scans to explore different brain activity between the specific and nonspecific effects of acupuncture.

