### MRI data acquisition

The MRI scan will be performed with a 3.0 Tesla superconductor (Skyra, Siemens, Erlangen, Germany) in the Beijing Hospital of Traditional Chinese Medicine Affiliated to Capital Medical University. Participants will undergo fMRI scans at baseline and the end of intervention. Before scanning, participants will be required to wear earplugs and headgear and remove all magnetic and metal items. The foam pad will be used to reduce head movement. Participants will be required to maintain a comfortable supine position and keep awake.

Scanning parameters: echo planar imaging (EPI) sequence will be used for resting fMRI scanning: repetition time (TR) = 2000 ms, echo time (TE) = 30 ms, field of view (FOV) = 224 mm × 224 mm, flip angle (FA) = 90°, layer thickness = 3.5 mm, axial slices = 32, size of voxel = 3.5 mm × 3.5 mm × 3.5 mm, in-plane resolution = 64 × 64, volumes = 240.

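### The imaging plan names a t test and repeated-measures ANOVA but no between-arm model with the baseline scan as covariate, which gives up precision on the two brain contrasts

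*Protocol article*

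**What the plan says.** The first purpose of the trial, at the end of the Background, is to "investigate the cerebral mechanism of the specific (true acupuncture vs sham acupuncture) and nonspecific effects (sham acupuncture vs waiting list) of acupuncture". The brain question is therefore two between-arm contrasts.

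Both scans are planned for everyone. MRI data acquisition says "Participants will undergo fMRI scans at baseline and the end of intervention", and Sample size says "Each participant will receive 2 fMRI scans to explore different brain activity between the specific and nonspecific effects of acupuncture". Allocation is "in a ratio of 1:1:1, with 30 participants in each group", and Sample size allows 20% for dropout and head motion.

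Neuroimaging data analysis plans that "T* test and repeated-measures analysis of variance will be conducted to investigate the differences in brain regions in each group". It does not say whether the t test is paired, on end scans or on change, or which ANOVA term answers the two contrasts. The only covariates it lists belong to preprocessing: "regression removal of covariates (head model parameters, cerebrospinal fluid, brain white matter, and the mean whole-brain signals". These are nuisance signals within a scan. None is the participant's baseline value of the measure being compared.

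**The concern.** A baseline scan helps a between-arm comparison to the extent that it predicts the end scan. The named tests do not let the data decide how much weight it gets. The group-by-time term subtracts the whole baseline value, so when the two scans correlate weakly it adds noise. A t test on end scans, if one is intended, gives baseline no weight and wastes it when the scans correlate strongly. ANCOVA estimates the weight.

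At stake is the chance of detecting a true-vs-sham or sham-vs-waiting-list difference in brain measures, with roughly 24 usable participants per arm. Imaging is the first stated purpose and the sole basis of the sample size, and the Discussion itself lists the small groups as a limitation.

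**Working it through.** **Inputs from the article.** Two scans per participant; 30 per arm; 20% loss; 25 participants as the stricter-threshold figure in Sample size; two-sided 0.05 (stated under Clinical data analysis).

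**Assumed inputs, because the article gives none.** Scan-to-scan correlation rho from 0.3 to 0.8; a between-arm difference of 0.6 SD; equal variance at both scans.

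**Step 1: the plan's own figure.** 25 × 1.2 = 30, the stated number per arm. (Dividing instead, 25/0.8 = 31.25, gives 32.) The 12 and 25 come from cited studies without an effect size or SD and cannot be rebuilt from the article. After 20% loss, 30 × 0.8 = 24 per arm; this is used below.

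**Step 2: what the ANOVA tests.** With two time points, the group-by-time F for a pair of arms equals the squared t statistic on change scores. In a simulated data set both were 10.9625. So this test does use the baseline scan, with slope 1.

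**Step 3: variance of a between-arm contrast**, in units of the outcome variance:
- t test on end scans: 1
- change score (group-by-time): 2(1 − rho)
- ANCOVA: 1 − rho²

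ANCOVA relative to change is (1 − rho²)/[2(1 − rho)] = (1 + rho)/2. Relative to end scans only, it is 1 − rho².

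| rho | End only | Change | ANCOVA | ANCOVA/change | ANCOVA/end only |
|---|---|---|---|---|---|
| 0.3 | 1.00 | 1.40 | 0.91 | 0.65 | 0.91 |
| 0.5 | 1.00 | 1.00 | 0.75 | 0.75 | 0.75 |
| 0.7 | 1.00 | 0.60 | 0.51 | 0.85 | 0.51 |
| 0.8 | 1.00 | 0.40 | 0.36 | 0.90 | 0.36 |

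**Step 4: cost of estimating the slope.** In 20,000 simulated trials with 25 per arm, the ANCOVA/change ratio was 0.67, 0.76 and 0.87 at rho 0.3, 0.5 and 0.7, against 0.65, 0.75 and 0.85 in theory. The penalty is about 0.01 to 0.02.

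**Step 5: power.** Noncentral t with noncentrality 0.6 × √(24/(2V)), where V is the variance from Step 3. Degrees of freedom are 46 for the two unadjusted tests and 45 for ANCOVA. At rho 0.5, for example, the noncentrality is 0.6 × √12 = 2.08 for the change score and 0.6 × √(12/0.75) = 2.40 for ANCOVA.

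| rho | End only | Change | ANCOVA | Gain over change |
|---|---|---|---|---|
| 0.3 | 53% | 41% | 57% | 16 points |
| 0.5 | 53% | 53% | 65% | 12 points |
| 0.7 | 53% | 75% | 81% | 6 points |
| 0.8 | 53% | 90% | 92% | 2 points |

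These figures are for a single comparison at 0.05. They illustrate the relative loss and do not predict the power of a whole-brain analysis.

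**The case against.** The strongest reply is that the plan already uses the baseline scan. Repeated-measures ANOVA takes it as one of its two measurements, and the Abstract and Discussion speak of changes in brain activity. The natural reading is within-group paired tests plus a group-by-time term, a valid and conventional analysis. This stands. A reader might infer that the planned tests ignore baseline altogether; the text does not support that. It would be true only of a t test on end scans, which the article never says is meant, so the large gains over that test (53% to 92% at rho 0.8) should not be quoted as the plan's loss. Nor does the article make the ANOVA group main effect the test of interest.

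Second, the gain over the change score shrinks as rho rises, and nothing in the article says that rho is low. This also stands, and is why the result is given as a range.

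Third, a reader might infer that change scores would create spurious treatment effects through chance baseline imbalance. Under randomisation the change-score test is unbiased and holds its error rate; what is lost is precision.

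Fourth, an article may leave model detail to the full protocol. That carries less weight here, because the article does not leave the method open: it commits to named tests, and a fuller plan would have to add to or depart from them.

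**Conclusion.** The concern holds as a point about efficiency. No baseline-adjusted between-arm model is named for the imaging measures, although the baseline scan is planned for all. Compared with the change-score test implied by the ANOVA, ANCOVA lowers contrast variance by 35% at rho 0.3, 25% at 0.5, 15% at 0.7 and 10% at 0.8, less the small slope penalty. The power gain runs from 16 points down to 2 under the assumptions above. Rho, the 0.6 SD difference and equal variances are assumptions; the direction does not depend on the size of the difference, but the number of points gained does.

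Which of the two unadjusted approaches would do better also depends on rho (end scans below 0.5, change above it), and rho is not known in advance. Apart from the slope penalty, ANCOVA does at least as well as either, so it removes that gamble. The point is confined to the imaging aim and does not bear on the NRS response rate.

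**What to change.** In Neuroimaging data analysis, state that the between-arm analysis of each imaging measure is an ANCOVA, voxel-wise or by region of interest. The outcome is the end-of-intervention value, arm is the factor, and the participant's own baseline value of the same measure is the covariate. Report acupuncture vs sham and sham vs waiting list from this model. Keep within-group paired t tests as descriptive.

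The cost is a sentence or two of wording, one residual degree of freedom per model and the small slope-estimation penalty. No extra scans or participants are needed. Participants without a usable baseline scan would be left out, as they would be from any change analysis. The change should be made before the imaging data are analysed.
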